## BACKGROUND

People with long COVID report 'push-crash' cycles, with a disproportionate worsening of

symptoms in response to activity, similar to post-exertional malaise (PEM) reported by patients with chronic fatigue syndrome. These PEM-like symptoms increase the overall symptom load, reduce each individual's quality of life, and make recovery harder.

Adaptive pacing has emerged as a common strategy to self-manage PEM-like symptoms. Our systematic reviews suggest adaptive pacing is effective in improving some symptoms in people with ME/CFS. However, recent work endorsed by our long COVID PPI group indicates that implementing adaptive pacing is often problematic for those attempting to self-manage. Difficulties include accurately estimating concepts such as energy availability and predicted energy use and identifying and tracking a suitable threshold to limit activity. Combining these requirements to plan daily activities, often hour by-hour, can be highly challenging, particularly when symptoms include impaired cognition.

This project aims to determine if combining continuous activity tracking with a just-in-time adaptive intervention (JITAI) can address these limitations. JITAIs provide information to participants at a time and context where they can act upon it. Widely used in behaviour change research, JITAIs are yet to be applied to adaptive pacing. Using a randomised control study design, we will allocate 250 participants to receive either JITAI supported adaptive pacing or usual care. Our primary outcome is PEM using the De Paul Symptom Questionnaire (DSQ)-PEM at baseline and 6 months.

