## **OBJECTIVES**

- To assess whether real-time activity alerts based on JITAI improve participants' ability to adhere to adaptive pacing strategies.

- To analyse retrospective activity data preceding PEM episodes to refine individual activity thresholds.
- To examine user experiences, feasibility, and adherence to the digital intervention for managing activity levels.
- To determine whether the intervention leads to a reduction in the frequency and severity of PEM episodes over time.

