## **HYPOTHESIS**

### *Primary Hypothesis*

**H0:** An activity tracking and personalised JITAI will not reduce symptoms of post-exertional malaise (PEM) in people with long COVID compared to usual care six months after randomisation.

**Ha:** There will be differences in symptoms of PEM in people with long COVID compared to a usual care group six months after randomisation in an activity tracking and personalised JITAI.

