### *App design and features*

To aid data collection the app also includes a series of validated instruments. As a result, in addition to logging a bout of PEM the app includes four 'sections' that participants will be requested to complete monthly: A 'symptom check in' to get a view of the month-by-month symptom load of participants. A 'brain-fog test' to assess cognitive function using the symbol digit modalities test. The remaining instruments will be split into two groups A and B, with

each group completed at a single point in time. Group A includes the Edinburgh Neurological Survey, the modified PEM questionnaire, and the SF12 quality of life assessment. Group B includes the MRC breathlessness scale, the EQ-5D-5L, PHQ4, the self-efficacy for long-term conditions, and the visual analogue pain scale. Data from each of the instruments will be stored in a GDPR-compliant data server. We also have the data server scan each participant's responses daily and send appropriate notifications to complete one of the four sections each week if responses are missing.

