### *Statistical methods*

All analyses will be conducted using Jamovi version 2.3.21. Data will be tested for normal distribution and homogeneity of variance to confirm parametric assumptions are met. Data will be presented in text and tables as means and 95% confidence intervals (CI) unless otherwise stated. Because of randomisation, we did not undertake analysis of baseline equivalence, since the null hypothesis must be true and any differences due to chance . Only participants who completed follow-up testing were included in analysis (i.e. per protocol analysis). The effect of the energy management intervention on main and secondary outcomes will be examined using two-way mixed-model ANOVA with condition (intervention or control) as the between-subjects factor and time (pre- and post-intervention) as a within subjects' factor. Alpha level will be reported as exact p values and not described dichotomously as 'significant' or otherwise as recommended by the American Statistical Association . We will express effect sizes from the ANOVA as partial eta-squared ( $\eta^2p$ ), with values of 0.01, 0.06, and 0.14 interpreted as small, moderate, and large, respectively . For categorical data, (DSQ-PEM questions 6-10) we will use McNemar's Test for paired samples (pre- to post- intervention), or Chi squared test for between group effects (intervention vs. control).

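### PEM scores are requested monthly and bouts logged in both arms, but the only stated efficacy model uses one pre and one post value in completers, so the objective on PEM episodes over time has no between-arm analysis

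*Protocol*

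**What the plan says.** **Timing of the primary outcome.** The Background measures the DSQ-PEM "at baseline and 6 months". The Primary Hypothesis concerns PEM symptoms "in people with long COVID compared to usual care six months after randomisation".

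**Model.** Under Statistical methods, effects "on main and secondary outcomes will be examined using two-way mixed-model ANOVA with condition (intervention or control) as the between-subjects factor". The second factor, which is repeated in each participant, has two levels only ("time (pre- and post-intervention) as a within"). The same section limits the analysis to those who completed follow-up testing. The sample size section likewise assumes two time points.

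**Data collected.** Under App design and features, "the app includes four 'sections' that participants will be requested to complete monthly". One section, Group A, holds the modified PEM questionnaire, cited to the same source (reference 15) as the DSQ-PEM (reference 9). Control participants receive the same four sections and can also log PEM bouts (Control participants).

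**Objective.** The fourth objective is "To determine whether the intervention leads to a reduction in the frequency and severity of PEM episodes over time".

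**The concern.** The Background describes push-crash cycles "with a disproportionate worsening of" symptoms after activity. The activity allowance is revised during the trial: it can be reduced after a reported bout and raised after three weeks without one (Activity allowance). An effect that changes over the six months is therefore plausible.

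A pre/post contrast cannot separate an early benefit that fades from one that builds, and it does not count episodes. It also discards anyone who supplied monthly scores but no final one. All of this information is already being requested from both arms. The model is fixed in the protocol itself, so the point concerns what is stated rather than detail left to a later analysis plan.

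**Working it through.** **1. Collection against analysis**

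| Item | Requested or logged | Stated between-arm analysis |
|---|---|---|
| DSQ-PEM at baseline and month 6 | both arms | two-way ANOVA, completers |
| Monthly DSQ-PEM in between | both arms | none |
| Logged PEM bouts | both arms | none; a supplementary figure shows PEM-free days per month with 95% CIs |

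The monthly reading needs one check, because App design and features also says each questionnaire group is completed at a single point in time. Read with the monthly request and the weekly prompts for one of four sections, this means one sitting per month, not one per trial.

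**2. The plan's own sample size.** Inputs: f = 0.25, two groups, two time points, alpha 0.05, power 0.90. For the interaction, λ = f²N, df1 = 1 and df2 = N − 2. At N = 170, λ = 0.0625 × 170 = 10.6 and power is 0.8999; N = 171 gives 0.9016. The stated 170 reproduces. The formula is equivalent to a two-sample comparison at d = 0.5 with SD 25 (85 per arm). That SD is the SD of change only if 2 × 25² × (1 − ρ) = 25², that is, ρ = 0.5 between baseline and follow-up.

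**3. Completers.** The demographics table gives 77 + 84 = 161, which is 161/250 = 64.4% of the planned total. The shortfall is 35.6%, against the 30% allowed for. Power at N = 161 by the same formula is 0.884. If 250 were randomised, 250 − 161 = 89 did not complete. The documents do not say how many of them supplied any monthly score.

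**4. Averaging months 4 to 6.** Assume equal SDs, baseline-follow-up correlation 0.5 and follow-up-follow-up correlation r. In units of SD², the change-score variance with the mean of k follow-ups is

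(1 + (k − 1)r)/k + 1 − 2 × 0.5 = (1 + (k − 1)r)/k.

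The 95% CI half-width at 85 per arm is 1.96 × 25 × √(factor) × √(2/85) = 7.52 × √(factor).

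| | Factor | Reduction | Half-width (points) |
|---|---|---|---|
| One follow-up | 1.000 | – | 7.5 |
| k = 3, r = 0.5 | 2.0/3 = 0.667 | 33% | 6.1 |
| k = 3, r = 0.6 | 2.2/3 = 0.733 | 27% | 6.4 |
| k = 3, r = 0.7 | 2.4/3 = 0.800 | 20% | 6.7 |

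**5. If the effect builds up.** Suppose, for illustration, that it rises linearly from 0 at baseline to 13 points at month 6. The months 4 to 6 mean effect is then 13 × (4 + 5 + 6)/(3 × 6) = 10.8, or 0.833 of the month-6 effect. At r = 0.6 the standard error falls to √0.733 = 0.856 of its single-visit value. The ratio of effect to standard error is then 0.833/0.856 = 0.97 of the month-6 ratio. The variance is still lower, but the gain in power is gone.

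**6. What reaches month 6.** Using baseline as a covariate in place of a change score takes the single-visit factor from 2 − 2ρ to 1 − ρ²: 1.40 to 0.91 at ρ = 0.3, 1.00 to 0.75 at 0.5, and 0.60 to 0.51 at 0.7. The extra months add to this mainly through participants whose month-6 score is missing.

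**The case against.** The strongest reply is that the plan is coherent: the Background, the Primary Hypothesis, the sample size and the model all point to baseline and six months, and a single landmark endpoint is a legitimate choice. That stands. Four stronger readings are tempting, and the documents do not support them.

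- **That the trial cannot say whether PEM fell.** The group-by-time interaction tests the between-arm difference in change to six months. The course in between and any comparison of episodes are what is missing.
- **That the month-6 score is a one-day snapshot distorted by a nearby crash.** The DSQ-PEM includes frequency items, which summarise a period. The documents give no figure for how far a score shifts near a crash.
- **That months 1 to 5 are wholly unused.** PEM-free days per month are plotted, and bout logs drive the allowance in the intervention arm. It is the monthly questionnaire scores that enter no stated comparison.
- **That more visits make the month-6 result 20% to 33% more precise.** With complete data and an unrestricted covariance, a group-by-month model gives essentially the month-6 contrast it would give without the other visits.

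Two practical objections also stand. A classical repeated-measures ANOVA on all months would lose further participants to listwise deletion. And averaged questionnaire scores do not count the episodes named in the fourth objective.

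**Conclusion.** The point holds in a limited form. The primary test is not wrong. The gaps are that intermediate scores enter no arm comparison, partial completers are dropped, and the objective on episodes over time has no matching between-arm analysis.

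The precision gain is 20% to 33% lower change-score variance for the months 4 to 6 average. It rests on assumed correlations (0.5 with baseline, 0.5 to 0.7 among follow-ups) and equal SDs. Its benefit for power also needs a roughly constant effect over those months. The number of partial completers who could be recovered is at most 89 if 250 were randomised, and is otherwise unknown.

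**What to change.** 1. **Primary.** Keep the between-arm difference at month 6. Estimate it from a likelihood-based mixed model for repeated measures (group by month, baseline DSQ-PEM as covariate) on all available monthly scores from all randomised participants. Do not use an ANOVA with listwise deletion.
2. **Supportive, scores.** Report the monthly profile by arm and the between-arm difference averaged over months 4 to 6, with 95% CIs.
3. **Supportive, episodes.** Compare logged PEM bouts, or PEM-free days per month, between arms with a count or mixed model. Account for the time each participant was actually logging, since a day without a report is not necessarily a day without PEM. Note that logging can change the allowance in one arm only, so reporting may differ by arm.

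**Cost.** No new data collection or participant burden. The protocol says only that monthly scores are requested, so completeness by month should be reported. Participants with no follow-up score add little, data deleted on request cannot be used, and the mixed model assumes data missing at random. Check that the named software can fit it. The months 4 to 6 average is a different quantity from month 6, so it supports the primary result and does not replace it. Because the document already shows completer numbers and a PEM-free-days figure, show the planned ANOVA alongside and label the additions as supplementary.

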#### *Primary Outcome*

The primary outcome of the study is post-exertional malaise (PEM), assessed in terms of its frequency, severity, and duration. This domain captures the impact of activity on symptom exacerbation, including the persistence of symptoms following exertion.

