### *Measurement tools*

#### *PRIMARY OUTCOME*

##### *De Paul Symptom Questionnaire – Post-exertional malaise (DSQ-PEM)*

The baseline date will be considered as the date of baseline data collection. The DSQ-PEM is a 10-item questionnaire. Questions 1-5 are measured on a five-point Likert scale with a 'frequency' domain (0 = none of the time, 1 = a little of the time, 2 = about half the time, 3 = most of the time, and 4 = all of the time) and a 'severity' domain. (0 = symptom not present, 1 = mild, 2 = moderate, 3 = severe, and 4 = very severe). Questions 6-8 and 10 are dichotomous yes/no responses, and question 9 asked 'if you feel worse after activities, how long does this last?' with six options:  $\leq 1$  h, 2-3 h, 4-10 h, 11-13 h, 14-23 h, or  $\geq 24$  h. The DSQ-PEM sum is the sum of questions 1-5 (frequency and severity), expressed out of 100.

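### PEM duration is named in the primary outcome but lies outside the powered score, and its six-level item is assigned to McNemar's test or an order-blind chi-square

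*Protocol*

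**What the plan says.** Four parts of the protocol bear on this point.

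- **Primary Outcome:** "The primary outcome of the study is post-exertional malaise (PEM), assessed in terms of its frequency, severity, and duration".
- **Measurement tools, DSQ-PEM:** "The DSQ-PEM sum is the sum of questions 1-5 (frequency and severity), expressed out of 100". Duration is a separate item, question 9, which asks "how long does this last?' with six options", running from 1 hour or less to 24 hours or more. The same paragraph leaves question 9 out of its list of binary items: "Questions 6-8 and 10 are dichotomous yes/no responses".
- **Sample size and statistical power:** the primary variable is the DSQ-PEM, with a 13-point difference on a 100-point scale and an SD of 25. The Background section also names the DSQ-PEM, at baseline and 6 months.
- **Statistical methods:** main and secondary outcomes go to a two-way mixed ANOVA. The remaining DSQ-PEM items, question 9 among them, are handled as one block, introduced by "For categorical data, (DSQ-PEM questions 6-10) we will use". Two tests are named for that block: McNemar's for change over time, and, as the second option, "or Chi squared test for between group effects (intervention vs. control". No other analysis of question 9 is given.

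**The concern.** There are two linked problems.

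First, the definition of the primary outcome and the powered variable do not match. Duration belongs to the first and is absent from the second. A reader cannot tell whether a result on duration would count as primary evidence.

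Second, the tests assigned to duration suit it poorly. The analysis section treats questions 6-10 as one block, although the measurement section says that only 6, 7, 8 and 10 are yes/no. McNemar's test in its standard form needs a paired binary response, and no cut-point for question 9 is given, so it cannot be run on that item as written. Even on a binary item, a before-after test within one arm does not estimate the difference between arms that the primary hypothesis concerns. The chi-square does compare arms, but it discards the ordering of the six options and the baseline answer, and it does not say whether PEM became shorter or longer.

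At stake is a weak and hard-to-read result on a feature that the protocol itself names as part of its primary outcome.

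**Working it through.** **1. The protocol's own figure.** Inputs from the sample size section: f = 0.25, two groups, two time points, alpha 0.05, power 0.90, interaction test.

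- Noncentral F with df1 = 1, df2 = n - 2 and noncentrality n × f². At n = 170 this is 170 × 0.0625 = 10.625, and power is 0.8999. At n = 171 power is 0.902.
- Cross-check with d = 0.5: 2 × (1.960 + 1.282)² / 0.5² = 84.1, so 85 per arm.
- Dropout: 170 / (1 - 0.30) = 243, which the planned 250 covers.

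The stated 170 reproduces. It refers to the 100-point score. No power figure is given for duration.

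**2. Where each component of the primary outcome goes.**

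| Component | Item | In the 0-100 sum? | Planned analysis |
|---|---|---|---|
| Frequency | Questions 1-5 | Yes | Mixed ANOVA |
| Severity | Questions 1-5 | Yes | Mixed ANOVA |
| Duration | Question 9, six ordered options | No | McNemar or chi-square |

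**3. What the chi-square costs on question 9.** The protocol gives no distribution for question 9, so these are assumptions: 85 per arm, follow-up data only, a proportional-odds shift between arms, alpha 0.05, 3,000 simulated trials per scenario. The three reference distributions, from shortest to longest duration, are:

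- uniform: 1/6 in each category;
- half in the top category: 0.05, 0.10, 0.15, 0.10, 0.10, 0.50;
- three quarters in the top category: 0.03, 0.05, 0.08, 0.04, 0.05, 0.75.

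The Pearson chi-square on the 2 × 6 table (5 df) was set against the Wilcoxon-Mann-Whitney rank test.

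| Distribution | Odds ratio | Chi-square power | Rank test power | Loss (points) |
|---|---|---|---|---|
| Uniform | 2 | 46.0% | 72.1% | 26 |
| Half in top | 2 | 44.0% | 70.0% | 26 |
| Three quarters in top | 2 | 32.4% | 56.8% | 24 |
| Uniform | 2.5 | 74.1% | 92.3% | 18 |
| Half in top | 2.5 | 72.4% | 91.7% | 19 |
| Three quarters in top | 2.5 | 57.0% | 81.9% | 25 |

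With no effect, the chi-square rejected in 3.9% to 4.4% of trials and the rank test in 4.6% to 5.0%. A repeat with another seed and 6,000 trials per scenario gave losses in the same range, 18 to 26 points, and chi-square error rates of 3.9% to 5.4%. So the chi-square keeps its error rate, and what it loses is power. With three quarters of answers in one category, more than 20% of expected counts fell below 5 in 65% to 98% of trials, so the usual large-sample conditions would often fail.

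**4. Analytic check.** A noncentrality of 10.51 gives 90% power on 1 df and 70.3% on 5 df. This is the same order of loss, without assuming a category distribution.

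**The case against.** A reader might infer that duration gets no valid treatment comparison at all. The protocol does not support that. It assigns the chi-square explicitly to differences between the arms, and a 2 × 6 chi-square between randomised arms is a valid test. Omitting baseline is not an error in a randomised comparison either; adjusting for it buys precision.

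A reader might also infer that significance in one arm and not the other will be presented as evidence of effect. Nothing in the text says so. McNemar is assigned to change over time, and the same section says p values will be reported exactly and not sorted into significant or not. A calculation of how often that misreading would mislead also depends heavily on assumption. With the same true change in both arms and 77 and 84 pairs (the completers in the demographics table), exactly one arm falls below 0.05 in about 50% of trials if 25% improve and 12% worsen, but in 10% at 15%/15% and 4% at 40%/10%. The protocol gives no such rates, and 50% is close to the maximum of 2p(1 - p), where p is the rejection probability in each arm. I therefore rest nothing on that figure.

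Finally, the primary variable is largely settled elsewhere. The Background, the DSQ-PEM description and the sample size section point to the 0-100 score, and the Aims, Objectives and Significance sections speak of frequency and severity only. That stands, and it makes the mismatch one of wording. It does not remove it: "assessed in terms of its frequency, severity, and duration" is the protocol's formal definition of the primary outcome. Nor does it make McNemar suit a six-level item.

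**Conclusion.** The point holds in limited form. Three things follow directly from the text: duration is in the stated primary outcome and not in the powered score; question 9 is grouped with yes/no items for a test that does not fit it; and no ordinal or baseline-adjusted comparison of duration between arms is planned.

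The planned chi-square is valid but inefficient, by about 18 to 26 points of power against a rank test in the scenarios above. Those figures rest on assumed category distributions, a proportional-odds shift and 85 per arm. For a consistent shift in one direction, only the direction of the loss can be taken as general. The powered analysis of the 0-100 score is not affected. The change should be made, but the trial's main test does not depend on it.

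**What to change.** - **Primary Outcome section:** state that the primary outcome is the 0-100 sum of DSQ-PEM questions 1-5 at 6 months, in line with the Background, DSQ-PEM and sample size sections. List duration (question 9) as a named secondary outcome.
- **Statistical methods, question 9:** take it out of the McNemar/chi-square group. Compare arms at 6 months with a proportional-odds model of the category on arm and baseline category, with a rank test if proportional odds is doubtful.
- **Statistical methods, questions 6-8 and 10:** state that the between-arm comparison is the test of treatment effect and that within-arm McNemar results are descriptive. The chi-square suits these items; logistic regression adjusted for the baseline response is an optional gain in precision.

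The cost is a few sentences and one standard model on data already collected, plus an assumption of proportional odds to check. No new data and no change in sample size are needed.

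### PEM duration (DSQ-PEM question 9, six ordered levels) is assigned to McNemar's test, which does not apply to it, or to a chi-squared test, which ignores its order and loses power

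*Protocol*

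**What the plan says.** Protocol, Primary Outcome, defines PEM as "assessed in terms of its frequency, severity, and duration".

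Protocol, Measurement tools (DSQ-PEM), describes the items. "Questions 6-8 and 10 are dichotomous yes/no responses", whereas "question 9 asked 'if you feel worse after activities, how long does this last?' with six options", running from 1 hour or less to 24 hours or more. The total score leaves duration out: "The DSQ-PEM sum is the sum of questions 1-5 (frequency and severity), expressed out of 100".

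Protocol, Statistical methods, treats questions 6 to 10 as one categorical group ("For categorical data, (DSQ-PEM questions 6-10) we will use") and assigns them "McNemar's Test for paired samples (pre- to post- intervention), or Chi squared test for between group effects". Question 9 is not excepted, and the section names no ordinal method. The only effect size it names is partial eta-squared from the ANOVA.

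**The concern.** The analysis rule treats five items alike, although the instrument description says that one of them is of a different kind. Question 9 has six levels with a natural order.

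- **McNemar's test** compares the two discordant cells of a paired 2x2 table. With six levels there is no such table unless someone chooses a cut-point, and the Protocol gives none. The extension to larger square tables (Bowker's symmetry test) is not named and also ignores order. Either way it is a pre-to-post test within one arm, so it does not compare treatments.
- **The 2x6 chi-squared test** is the between-arm comparison. It treats the six durations as labels and uses 5 degrees of freedom. Shuffling the hour bands would leave its p-value unchanged, so it cannot say whether PEM became shorter or longer. It also makes no use of the baseline answer.

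At stake is the one DSQ-PEM item described as measuring duration. Its analysis would yield a p-value with no direction or effect size, from a test weaker than the same answers allow.

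**Working it through.** **1. The plan's own figure.** Sample size and statistical power uses f = 0.25, two groups, two time points, alpha 0.05 and power 0.90, and reports 170 in total (85 per group). For the interaction, the noncentrality is f² × N = 0.0625 × 170 = 10.625 on 1 and 168 df, which gives power 0.8999. A two-sample calculation with d = 0.5 also gives 85 per arm. Allowing for 30% drop-out, 85/0.7 rounds up to 122, so 125 is adequate. The figure reproduces. It concerns the DSQ-PEM sum, and the Protocol gives no power, expected effect or answer distribution for question 9. Everything below therefore rests on stated assumptions.

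**2. Cost of the extra degrees of freedom.** Suppose the whole signal lies along the ordered contrast. A 1-df test at two-sided 0.05 needs noncentrality λ = (z₀.₉₇₅ + z_power)².

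- 80% power: λ = (1.960 + 0.842)² = 7.85. A 5-df chi-squared test with the same λ has 55.5% power.
- 90% power: λ = (1.960 + 1.282)² = 10.51. The 5-df test has 70.3% power.

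To match the 1-df test, the 5-df test needs 1.63 times the sample at 80% power and 1.57 times at 90%.

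**3. Simulation at the reported completer numbers.** Participant demographics gives 77 control and 84 intervention completers. Three control distributions over the six levels were assumed:

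- A: uniform
- B: 5/8/12/10/15/50%
- C: 2/4/7/5/7/75%

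The intervention arm was shifted to shorter durations by a common odds ratio (OR). Pearson chi-squared was compared with the tie-corrected Wilcoxon rank-sum test at two-sided 0.05, with 6,000 runs per case. Cells show chi-squared / rank-sum rejection rates in percent.

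| OR | A | B | C |
|---|---|---|---|
| 1.0 | 5.1 / 5.0 | 4.6 / 4.9 | 4.1 / 5.5 |
| 1.5 | 16.1 / 30.4 | 14.8 / 28.9 | 9.7 / 21.3 |
| 2.0 | 43.5 / 70.5 | 40.4 / 67.8 | 28.6 / 54.0 |
| 2.5 | 69.9 / 89.7 | 68.3 / 88.3 | 53.1 / 81.0 |
| 3.0 | 86.6 / 97.4 | 85.5 / 96.8 | 73.9 / 92.8 |

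The differences are 27.0, 27.4 and 25.4 points at OR 2.0, and 19.8, 20.0 and 27.9 points at OR 2.5. Other assumed distributions move the ranges by only a few points, for example to 31-42% against 57-69% at OR 2.0 and 52-68% against 80-89% at OR 2.5.

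**4. Which row corresponds to the design effect.** On logistic scaling, d = 0.5 corresponds to OR = exp(0.5 × π/√3) = exp(0.907) = 2.48, close to the 2.5 row. There the chance of missing the shift is 30-47% with chi-squared (100 − 69.9 to 100 − 53.1) and 10-19% with the rank test.

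**5. Sparse cells.** With no effect, the share of tables with at least one expected count below 5 was 0% under A, 89% under B and 100% under C. It depends entirely on how far answers cluster in one level and leave other levels thin.

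**The case against.** The case on the other side has several parts.

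- **Missed effects.** A reader might infer that a real shortening of PEM is likely to be missed. The documents do not support that. They give no distribution or effect for question 9. At a shift of about the design size, chi-squared still rejects more often than not in every case simulated. At OR 1.5 the rank test usually fails as well. Statistical methods also reports exact p-values without a significant/not significant label, so the loss appears as weaker evidence. This objection stands.
- **Validity.** A reader might infer that the chi-squared test is invalid. It is not: its rejection rate under no effect was about 4-5%. Only McNemar's test is inapplicable as named. This stands.
- **A favourable comparison.** The simulation assumes proportional odds, and the analytic check puts all the signal on the ordered contrast. Both favour the ordered test. That limits how exactly the loss can be stated, but an ordered shift is the effect of interest for a duration.
- **Sparse cells.** A general claim of sparse tables is not supported, as step 5 shows. This stands.
- **Weight of the item.** Duration belongs to the stated primary outcome, but the trial is sized on the DSQ-PEM score, which is defined from questions 1-5, and Outcomes and Significance speaks only of frequency and severity. The main ANOVA is untouched. Nor can one be sure that question 9 is the only duration measure, because the wording of questions 6-8 and 10 is not given.
- **Limits of an ordinal analysis.** Question 9 is conditional ("if you feel worse after activities, how long does this last") and its six listed options include no level for absent PEM. An ordinal model does not solve that.

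None of this rescues the rule for question 9. A separate analysis plan might refine it, but the Protocol itself assigns these tests.

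**Conclusion.** The concern holds in a limited form. As written, McNemar's test does not apply to question 9. The between-arm chi-squared test is valid but ignores order, and it yields no direction or effect estimate. Under an assumed proportional-odds shift with 77 and 84 completers, it gives up roughly 20-28 points of power for moderate effects (odds ratios of 2.0 to 2.5), and less for smaller or larger ones in most cases simulated. Those figures depend on assumed answer distributions, since the Protocol supplies none. Sparse cells are a problem only if answers cluster in one level. The analysis of the powered DSQ-PEM sum is unaffected, so this is a correction that should be made to one component of the primary outcome and not a threat to the main result.

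**What to change.** Limit the McNemar/chi-squared sentence in Statistical methods to questions 6-8 and 10. For question 9, compare the arms at six months with a proportional-odds (ordinal logistic) model containing arm and baseline question 9, and report the common odds ratio with its 95% CI. If proportional odds is doubtful, use a Wilcoxon-Mann-Whitney test. State alongside it how participants who report no PEM enter the analysis.

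The main change is one sentence of text and needs no new data. The small downside is the proportional-odds assumption, for which the rank test is the fallback. The Protocol document already tabulates completers and presents some results, so if question 9 has been analysed, the ordinal analysis should be labelled as a reanalysis.
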